### Sample size

Because this is the first study in which the clinical effects of hypoxia therapy will be measured in PD and because of the study’s exploratory nature, a formal sample size calculation cannot be performed. A previously published power and sample size simulation study aggregated N-of-1 trials with multiple cycles of intervention and placebo per participant, and found that under certain assumptions N-of-1 trials needed only one-third of the sample size of an RCT to reach a similar power and type I error [36]. This was confirmed in a recent aggregated N-of-1 trial that investigated the effectiveness of the drug mexiletine in myotonia, in which the aggregated N-of-1 trial showed comparable treatments effects on a personalized Likert scale (i.e., the same outcome measure as we propose) with inclusion of 11 participants vs 57 participants in a traditional cross-over RCT [32]. Our proposed sample size of 20 was motivated by this work, in combination with the sample size consensus for feasibility studies of 20–30 [37].

The observed effect sizes and standard deviations of the different hypoxia protocols that are found to be clinically meaningful at the participant group level in this study (*N* = 20) will be used to simulate a power and sample size calculation for a future follow-up study that will be powered for efficacy using the data generated in this study.

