### Intervention

We will study the response to multiple exposures of different pre-selected hypoxia protocols per participant, as at present there is no conclusive evidence for the effect of different hypoxia stimuli. This will optimize the chances for any changes in outcomes being identified, and allowing the possibility of defining the optimal dose of hypoxia as a therapeutic intervention individually. The selection of interventions was based on multiple studies that investigated and reviewed the hypoxia regimes that are currently perceived as being most effective [38–43]. In this N-of-1 trial design, every participant will receive two sets of five different conditions, with one being the placebo and the other four variants of an active intervention, consisting of either intermittent or continuous hypoxia at FiO2 0.127 (~ 4000 m) and 0.163 (~ 2000 m). All interventions are administered twice to enhance intra-individual discriminative power towards a sufficiently low or high probability (see *Statistical Analysis*). As it is shown that hypoxic preconditioning effects may linger for up to four days [44], a wash-out of at least five days between sessions will be built-in. Once a week, one of the following five conditions will be administered following the order resulting from a Latin square randomization (see *Statistical Analysis*):

Active interventions:Continuous hypoxia for 45 min, at ~ 2000 m (16.3% O_2_)Continuous hypoxia for 45 min, at ~ 4000 m (12.7% O_2_)Intermittent hypoxia with 5 × 5-min at ~ 2000 m (16.3% O_2_), interspersed with 5-min normoxic recoveryIntermittent hypoxia with 5 × 5-min at ~ 4000 m (12.7% O_2_), interspersed with 5-min normoxic recoveryPlacebo intervention:Continuous normoxia for 45 min (20.9% O_2_)

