The intervention will be performed at Radboud university medical center in Nijmegen, the Netherlands. A commercially available hypoxicator will be used to deliver the hypoxic bout (*B-cat High Altitude*, the Netherlands). The hypoxicator (as an oxygen concentrator) is ISO 13485:2016 certified and uses a process called *pressure swing adsorption* to filter ambient air and to extract oxygen from that air. The principle is widely used in oxygen concentrators, but is inversely applied in the case of hypoxicators. Instead of oxygen-rich air, the resultant hypoxic gas is administered to the patient [45]. The hypoxicator is connected via medical-grade tubes to two large (> 50L) reservoir air bags that buffer the hypoxic gas mixture, which optimizes stability of the delivered FiO2. Intermittent hypoxia and the placebo situation is administered by switching a three-way Hans Rudolph® valve to either room air or the hypoxic circuitry. The intraday and between-day reliability of the hypoxicator were tested on multiple days before application in participants. Intraday variability was low (average range 0.2 percent points around desired FiO2) and between-day variability was within 0.1 percent points of desired FiO2. Seven days before the start of the first intervention, a one week at-home registration of self-reported outcomes of symptom severity will be conducted by a short daily morning survey. This assures a solid baseline of symptom severity that will be used in the Bayesian analysis (see *Statistical Analysis*).

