### Secondary outcomes

#### Self-reported outcomes

In this exploratory study, we will use a battery of outcomes to determine which symptoms or signs might respond to hypoxia. In accordance with accepted N-of-1 trial design recommendations and previously conducted trials [32, 50, 51], we have chosen to predefine personalized (self-reported) outcomes for each individual, scored on a 10-point Likert scale. Contrary to standardized PD scales, these outcomes better reflect important effects for the individual, and are potentially more sensitive to subtle treatment effects, reducing the risk of type II errors. Therefore, we included three participant-rated outcomes that assess on a 10-point Likert scale (allowing half points) general symptom impression, the urge to take a next dose of dopaminergic medication and the effect on one specific symptom that participants can choose themselves, based on goal attainment scale principles (Table 3). This symptom must fulfill the following criteria: it must fluctuate in severity throughout the day or between days, changes in its severity should be swiftly apparent and, if applicable, it is a symptom that previously improved at high altitude. To ensure a baseline score on these outcomes, participants will report these on a daily basis in the morning (in OFF) during the baseline period, i.e. 7 days preceding the start of the intervention period. On intervention days, participants will report these self-reported outcomes pre-intervention, directly post-intervention, 30 min post-intervention and from that moment on, another five times, on an hourly basis. In addition, these will be measured once every morning (i.e. in OFF) for the next three mornings after the intervention.

**Table 3 Tab3:** Secondary outcomes

Self-reported outcome variable	Researcher	Participant	Moment of measurement (in addition to baseline)	Measurement unit
**General symptom impression**		X	Directly after intervention and post-intervention 30 min, 1 h, 2 h, 3 h, 4 h and 5 h, and once every morning on the next three days	10-point Likert scale allowing half points
**Urge for dopaminergic medication** on the usual moments of intake		X	Directly after intervention and post-intervention 30 min, 1 h, 2 h, 3 h, 4 h and 5 h, and once every morning on the next three days	10-point Likert scale allowing half points

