### Secondary study parameters

#### Bayesian analysis

We will use a Bayesian model for the analysis of individual and aggregated N-of-1 trial results. This model allows for a direct estimation of the posterior probability that a treatment results in a clinically beneficial effect [32, 71–73]. The treatment effects resulting from the four different hypoxia protocols will be estimated per level of interest (i.e. the individual and group level). Every secondary outcome scored using the 10-point Likert scale will be modeled assuming a normal distribution centered around the patient’s true mean and variance for each protocol. If the posterior probability of reaching a 0.75-point difference between the secondary outcome after treatment and at baseline is greater than 80%, treatments are considered effective. Treatments are considered ineffective if the same posterior probability is less than 20%. Every treatment day has its own baseline (pre-intervention tests are performed) in order to further reduce period effects. The minimal clinically important difference for the secondary outcome MDS-UPDRS part III and Mini-BESTest is 4. One additional analysis will be performed including baseline characteristics and effect modifiers (see *Assessor-rated outcomes)* as covariates. Bayesian analyses will be performed using *JAGS* version 3.4.1 [74], run from *R* [75] using the package *rjags* [76].

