#### Frequentist analysis

For comparison with the Bayesian analysis we will also perform an explorative analysis of the secondary outcomes. For those that are normally distributed, we will use dependent *t* tests to calculate mean treatment effects, significance levels, and confidence intervals on group level. *P* values are 2-sided, and *P* < 0.05 will be the threshold for significance for all tests. Analyses will be performed using *R* [75]*.*

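### Every session has a pre-intervention score, but no described analysis uses it as a covariate, and the article leaves open which baseline the 0.75-point efficacy rule refers to

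*Protocol article*

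**What the plan says.** - **Design.** In the Intervention section under Methods/Design, "every participant will receive two sets of five different conditions", one of the five being placebo. That makes ten sessions per person and 200 in total for 20 people. A pre-intervention assessment precedes each session (Study procedures, Intervention; Self-reported outcomes).
- **Efficacy rule.** In the Bayesian analysis section a treatment is effective "If the posterior probability of reaching a 0.75-point difference between the secondary outcome after treatment and at baseline is greater than 80" per cent, and ineffective if the same probability is below 20%. The rule has no placebo term.
- **Baseline, first description.** The same section says: "Every treatment day has its own baseline (pre-intervention tests are performed) in order to further reduce period effects".
- **Baseline, second description.** The Intervention section says of the one-week home registration before the first session: "This assures a solid baseline of symptom severity that will be used in the Bayesian analysis". Under Self-reported outcomes, "participants will report these on a daily basis in the morning (in OFF) during the baseline period", meaning those same seven days.
- **Covariates.** "One additional analysis will be performed including baseline characteristics and effect modifiers". The Assessor-rated outcomes section lists these as age, gender, H&Y, PDQ-39, other medication, levodopa-equivalent dose, sleep quality and physical activity. The pre-session outcome score is not among them.
- **Frequentist analysis.** Dependent t tests are used "to calculate mean treatment effects, significance levels, and confidence intervals on group level". The text does not say whether the pair is active and placebo or post and pre, or whether change or post scores are compared.

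**The concern.** The only role for baseline that the article describes is as the reference point of a raw difference. Subtraction fixes the pre-post slope at 1. Across sessions within one person the slope is usually smaller, and subtraction then adds noise. If rho is below 0.5, a change score is noisier than the post-session score alone. The same-day score is already collected and could be used with an estimated slope instead.

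The reference point is also unsettled. The diary gives one home-based value per person, while the pre-session score gives ten hospital-based values. If the diary mean were subtracted, a systematic difference between scoring at home and in hospital would count towards or against the 0.75 points.

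With 20 people and two sessions per protocol, precision bears on whether a posterior probability clears 80% or stays undecided between 20% and 80%. It also bears on the effect sizes and SDs that the Sample size section intends to carry into the follow-up trial.

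**Working it through.** The plan has no power figure to reproduce: "a formal sample size calculation cannot be performed".

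**Inputs from the article:** 20 participants, two sessions per condition, ten sessions each, two-sided 5% tests, threshold 0.75 points.

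**Assumptions (not in the article):** within-person session SD s of 1.25, rho from 0.3 to 0.9, and SD tau of the treatment effect between people of 0 or 1.0.

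**Step 1. Variance per session for a contrast with placebo**
- change score: 2s²(1 − rho)
- post-session score only: s²
- adjusted for the same-day pre-score: s²(1 − rho²)

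The ratio of adjusted to change is (1 + rho)/2, and of adjusted to post-only is 1 − rho².

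| rho | adjusted / change | adjusted / post-only |
|---|---|---|
| 0.3 | 0.65 | 0.91 |
| 0.5 | 0.75 | 0.75 |
| 0.7 | 0.85 | 0.51 |
| 0.9 | 0.95 | 0.19 |

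A simulation with participant effects and a pooled slope (20 people, 10 sessions, 4,000 runs per rho, s = 1) agreed. Adjusted/change ratios were 0.65, 0.75, 0.86 and 0.96. All three estimators were unbiased for the placebo contrast.

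**Step 2. Power for that contrast**

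With v the per-session variance and two sessions per condition, SE = √[(2v/2 + tau²)/20] = √[(v + tau²)/20]. Power is from the noncentral t with 19 df, effect 0.75.

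At s = 1.25 and rho = 0.5, v is 2 × 1.5625 × 0.5 = 1.5625 (change) and 1.5625 × 0.75 = 1.1719 (adjusted).
- tau = 0: SE 0.280 against 0.242; power 72% against 84%.
- tau = 1.0: SE √(2.5625/20) = 0.358 against √(2.1719/20) = 0.330; power 51% against 58%. The variance saving is 1 − 2.1719/2.5625 = 15%.

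Other values at s = 1.25:
- rho 0.3, tau 0: change 58%, post-only 72%, adjusted 76%.
- rho 0.7, tau 0: change 91%, post-only 72%, adjusted 95%.
- rho 0.7, tau 1.0: change 63%, adjusted 66%.

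**Step 3. The rule as worded (pre-to-post change within one protocol)**

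Raw change over two sessions has variance s²(1 − rho). Evaluated at the person's mean of ten pre-scores, with the slope treated as known, it is s²[(1 − rho²)/2 + (1 − rho)²/10]. The ratio is (1 + rho)/2 + (1 − rho)/10, which gives 0.72, 0.80, 0.88 and 0.96 at rho 0.3, 0.5, 0.7 and 0.9.

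**Step 4. Individual results (one person, active against placebo, s = 1)**
- Slope estimated within that person: residual df fall from 5 to 4. The 95% half-widths, change against adjusted, are 3.07 and 3.07 at rho 0.3, 2.56 and 2.73 at 0.5, 1.98 and 2.25 at 0.7, and 1.14 and 1.37 at 0.9. There is no gain.
- Slope pooled over participants (3,000 runs): the SD of the estimate is 1.18 against 0.96, 1.00 against 0.87, 0.78 against 0.72, and 0.45 against 0.44. There is a gain, provided the slope is common.

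**The case against.** **The two baselines may not conflict.** The Intervention section says the diary will be used, not that it is the value subtracted. The remark that day-specific baselines reduce period effects further fits a model using both. This stands: a reader might infer a flat contradiction, but the text shows an ambiguity. Still, the rule that decides effectiveness refers to one baseline, and the article does not say which.

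**A condensed article need not specify the full model.** That is fair. The article does not state how baseline enters the Bayesian likelihood, so subtraction is read from the decision rule. But the article itself fixes a difference rule, lists the covariates and describes two baselines. Those statements can be reviewed.

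**The gain for a placebo contrast does not measure the quoted rule,** which contains no placebo term. This also stands. Step 3 shows that adjustment helps the within-protocol change too, by a smaller factor. The placebo-contrast figures apply only once the effect is restated against placebo, which changes the quantity estimated.

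**The power gain assumes one effect for everybody.** The Study population section stresses heterogeneity and mixes people who improved at altitude with at least five who had no such experience. Variation in effect between people is not removed by this covariate. The 12-point gain (72% to 84%) is therefore the case with no such variation. At tau = 1.0 it is about 7 points.

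**Two further stronger readings are not supported.** One is that the planned t tests lose a known amount of power; they do not say whether change or post scores are used, so no single figure applies. The other is that adjustment is free; it needs a slope shared across people, and a person-specific slope gives the individual results nothing.

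**Conclusion.** The concern holds in limited form. No listed analysis uses the same-day pre-session score as a covariate, although it exists for every session, and the baseline for the 0.75-point rule needs to be reconciled between the Intervention and Bayesian analysis sections.

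The direction of the gain is robust. For rho between 0 and 1, the adjusted session-level variance is below that of both change and post-only scores, apart from the small cost of estimating one pooled slope. The size is not known, because the article gives neither rho nor an SD. Against change scores the saving runs from 35% at rho 0.3 to 5% at rho 0.9; against post-only scores it is rho², or 9% to 81%. Variation in effect between people dilutes both.

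The outcomes concerned are secondary and the study is exploratory. The planned analyses are not shown to be biased for the placebo contrast; what is at stake is efficiency and an undefined reference point.

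**What to change.** 1. In the Bayesian analysis section, name the same-day pre-session score as the one baseline for the 0.75-point rule. Reword the Intervention section so that the 7-day diary mean is at most a person-level covariate.
2. State the effect to which the rule applies as active protocol versus placebo, and say that this replaces the within-protocol change.
3. In the Bayesian and frequentist group analyses, model the post-session score on condition, a participant effect and the same-day pre-score, with one within-person slope pooled over participants and protocols. If individual results are adjusted too, use the pooled slope and state the assumption.
4. Do the same for the assessor-rated outcomes that have pre-session tests.
5. Report the estimated slope and the between-person SD of the effect, since both are needed for the follow-up simulation.

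The cost is revised wording and one extra parameter, estimated from about 200 sessions, plus the common-slope assumption. No new data are required.

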#### Mechanistic markers

Lastly, three markers will be measured in serum, which serve as a hypothesis-generating addition to our study. These measures may provide insight into potential pathways involved in the (individual) responses to hypoxia in our study. These measures include platelet-derived growth factor receptor β (PDGFRβ), cortisol and erythropoietin (EPO).

PDGFRβ is a pericyte-shedded marker in response to hypoxia [59–62] and is associated with blood–brain barrier (BBB) permeability [60, 61, 63–65]. Disruption of the BBB is a central process involved in PD pathophysiology [66] and therefore, acute effects of hypoxia therapy on PDGFRβ would give insight in the influence that hypoxia might have on BBB integrity in the long term [65].

Cortisol is a marker of physiological and mental stress and is hypothesized to rise during systemic hypoxic challenges [67]. As stress is one of the main determinants of variations in symptom severity, we investigate whether cortisol release might be associated with the short-term symptomatic efficacy of hypoxia-based interventions. This will give insight in whether hypoxia has beneficial influence on the stress system, or that the physiological stress results in fatigue and mental stress, thus worsening PD symptoms in the short-term. Cortisol is measured twice pre-intervention and three times post-intervention, because of its concentration changing with circadian rhythm.

EPO is a protein that is primarily shedded peripherally by the kidney. Although it is employed as a marker of hypoxic dose, attention for its role in neuroprotection has risen in recent years [68]. In preclinical PD models, it prevents neurotoxicity and preserves neuronal functioning [69, 70].

All outcome measures are summarized in further detail in Supplementary Fig. 1.

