Hypoxia-based therapy has been applied extensively in research in a wide spectrum of healthy participants and individuals with medical conditions, and both short- and long-term effects have been investigated. Examples of previously studied treatment goals in various populations include rehabilitation in spinal cord injury (SCI) [55, 77–81], cardiorespiratory control in type I and II diabetes [82, 83], endurance and exercise tolerance and performance in healthy and geriatric individuals [24, 25, 27, 29, 84, 85], cognitive performance in geriatric and elderly individuals [22, 26, 28, 86], cardiovascular risk factors in obese individuals [87], reducing acute mountain sickness [88], and training of respiratory dysfunction [42, 48, 89–91]. However, clinical parameters or symptomatic efficacy of hypoxia-based therapy have thus far never been studied in PD, even though the aforementioned underlying working mechanisms of hypoxia would make PD an attractive disorder to study. One earlier brief report investigated the effects of (unspecified) IHT on the hypoxic ventilatory response in PD and found markedly reduced hypoxic ventilatory response, indicating a suboptimal response in breathing frequency to hypoxic challenges [48]. Because there is such limited previous experience with delivering hypoxia to persons with PD, several theoretical concerns must be addressed in this study proposed here. First, because respiratory abnormalities can already be observed in relatively early stages of PD [92], the safety and feasibility profile of different hypoxia protocols must be established first; this is one of the goals of the present study. Second, the short-term as well as long-term effects should be investigated separately, as different mechanisms might be involved [[name] et al., manuscript in preparation]. With regard to short-term effects, we might counter both beneficial and harmful effects (such as stress, increased oxidative stress), and the hypoxic dose for which this balance is optimal remains to be established in PD.

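### The Bayesian decision rule has no category for clinically relevant worsening, so a hypoxia protocol that aggravates symptoms shares the label 'ineffective' with one that does nothing

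*Protocol article*

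**What the plan says.** The section headed Bayesian analysis (under Secondary study parameters) introduces the quantity of interest as follows: "This model allows for a direct estimation of the posterior probability that a treatment results in a clinically beneficial effect". It then fixes two verdicts. When this "posterior probability of reaching a 0.75-point difference between the secondary outcome after treatment and at baseline is greater than 80%, treatments are considered effective". The other verdict is "Treatments are considered ineffective if the same posterior probability is less than 20" per cent. Between 20% and 80% neither label applies. Effects are to be estimated for each of the four hypoxia protocols, at individual and at group level.

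For two assessor-rated scales the section adds a threshold: "The minimal clinically important difference for the secondary outcome MDS-UPDRS part III and Mini-BESTest is 4".

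Two other places bear on worsening. Under Mechanistic markers, the cortisol rationale weighs a beneficial influence on the stress system against the alternative that "the physiological stress results in fatigue and mental stress, thus worsening PD symptoms in the short-term". The Discussion says "With regard to short-term effects, we might counter both beneficial and harmful effects", and that the hypoxic dose at which this balance is best is still unknown in Parkinson's disease.

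Table 2 (primary outcomes) lists adverse events, self-reported dizziness, discomfort and stress, vital signs and the feasibility questionnaire. It contains no Parkinson symptom score.

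**The concern.** A rule built on the probability of improvement alone cannot separate 'no effect' from 'worse'. Both give a low probability of improvement, and both therefore end in the same verdict.

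This matters more here than in a late efficacy trial. The study is a first assessment of safety and feasibility in this population. It compares four active protocols within each participant, and its Intervention section hopes to define the best dose individually. A protocol with no effect and one that makes a participant's symptoms clinically worse have different implications for that choice and for the design of the follow-up study. The published classification does not tell them apart.

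**Working it through.** The article states no operating characteristics for the rule, and its Sample size section says that no formal calculation was possible. There is therefore no figure of the plan's own to reproduce. The check applies the rule to a normal posterior for the change.

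**Inputs.** The threshold of 0.75 points and the limits of 80% and 20% come from the Bayesian analysis section. The posterior SD *s* is an assumption, because the article gives none; the range used is 0.3 to 1.0 points. The mean change *m* is positive for improvement.

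**Formulas.**
- Probability of improvement (the stated rule): P(change ≥ 0.75) = 1 − Φ((0.75 − m)/s)
- Mirrored probability of worsening (not in the plan): P(change ≤ −0.75) = Φ((−0.75 − m)/s)

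**A single example, s = 0.5.**
- Worsening of 1.0 point: 1 − Φ((0.75 + 1.0)/0.5) = 1 − Φ(3.5) = 0.0002, labelled ineffective.
- Null effect: 1 − Φ(0.75/0.5) = 1 − Φ(1.5) = 0.067, labelled ineffective.

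**Over the range of s.**

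| s | Improvement, m = 0 | Improvement, m = −1.5 | Worsening, m = 0 | Worsening, m = −1.5 |
|---|---|---|---|---|
| 0.3 | 0.006 | <0.0001 | 0.006 | 0.994 |
| 0.5 | 0.067 | <0.0001 | 0.067 | 0.933 |
| 0.75 | 0.159 | 0.001 | 0.159 | 0.841 |
| 1.0 | 0.227 | 0.012 | 0.227 | 0.773 |

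A worsening of 1.5 points is labelled ineffective at every SD shown. A null effect gets the same label as long as 0.75/s exceeds 0.8416, that is, for s below 0.75/0.8416 = 0.89. Above that the null becomes undetermined while the worsening protocol is still called ineffective.

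**What a mirrored category would do.** With an 80% limit, a worsening of 1.5 points is flagged for s up to 0.75 and is undetermined at s = 1.0. A worsening of 2 points is flagged even at s = 1.0: Φ(1.25) = 0.894. A null effect is never flagged. A worsening of 1.0 point at s = 0.5 gives Φ(0.5) = 0.69: it loses the label 'ineffective' and becomes undetermined, but is not called worsened.

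**The case against.** The best defence is that 'ineffective' is an efficacy label on secondary outcomes in an exploratory trial, and is not false for a protocol that does harm. The label also does not stand alone. Effects are estimated per individual, so worsening would show as an estimate in the wrong direction. The Frequentist analysis section adds two-sided tests with confidence intervals at group level. Adverse events are reported, and the data safety monitoring board sees secondary outcomes at the second interim analysis. The worsening foreseen under Mechanistic markers is only one of two alternatives, and the harms that the Discussion gives as examples are stress and oxidative stress rather than Parkinson symptoms.

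Most of this stands, and it means that harm is not wholly hidden. It does not close the gap. The group tests are limited to normally distributed outcomes, and opposite individual responses can cancel in a mean. Whether aggravated symptoms count as an adverse event depends on a definition that is not shown. None of these routes classifies worsening for an individual, which is the level at which the rule is meant to work.

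A reader might go further and infer that the rule has no direction, so that a worsening protocol could be called effective, because the operative sentence speaks only of a difference. The document does not support that. The same paragraph has already named the quantity as the probability of a clinically beneficial effect. Even if the sentence is taken alone, the result depends on the assumed SD: for a worsening of 1.0 point, the probability of an absolute change of at least 0.75 is 0.84 at SD 0.25 but 0.69 at SD 0.5, which is below the limit. Scale anchors and sign coding may also be set out in the full protocol or analysis plan. Direction is a matter of wording only.

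It is also fair that a mirrored category based on change from baseline could mistake drift during an OFF-state session for harm from hypoxia. The fix has to deal with that.

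**Conclusion.** The point holds in a limited form. On the reading its paragraph intends, the rule has no category for clinically relevant worsening, and it gives a harmful protocol the same verdict as an inert one. At an assumed posterior SD of 0.5 the two improvement probabilities are 0.0002 and 0.067, both well under 20%. The label for a 1.5-point worsening does not depend on the SD between 0.3 and 1.0; the label for the null does, and changes at about 0.89.

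The calculation assumes a normal posterior and SDs that the article does not give. Each protocol is given only twice per participant, so individual SDs may lie towards the upper end of the range. There the mirrored category will more often replace 'ineffective' by 'undetermined' than by 'worsened'.

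This is an inexpensive improvement to the classification. It is not evidence that harm would go unseen.

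**What to change.** In the Bayesian analysis section:

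- Word the rule as an improvement of at least 0.75 points, and state the better direction for each outcome.
- From the same posterior, report the probability of a worsening of at least 0.75 points. For MDS-UPDRS part III and Mini-BESTest, use at least 4 points in the worse direction. The article gives 4 only as the minimal clinically important difference, so the section should also say whether it replaces 0.75 in the rule for these scales.
- Report this for each hypoxia protocol at individual and group level. Label it 'worsened' above 80%, and keep 'ineffective' for cases where the improvement and worsening probabilities are both below 20%.
- Show the same two probabilities for the placebo sessions, so that drift within a session in the OFF state is not read as an effect of hypoxia.
- Report the 'worsened' verdicts beside the safety results.

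The cost is a change of wording and further summaries of the posterior, with the placebo condition included in the same output. No new data or visits are needed. The downside is one more verdict category, and some results will move from 'ineffective' to undetermined, such as the 1.0-point worsening at SD 0.5 with a worsening probability of 0.69.
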